#### Secondary study parameter(s); indirect clinical effectiveness

Three-level MLA will also be used to study the relative efficacy of CBT-E versus TAU in reducing scores on the secondary outcome measures.

#### Putative mediators

To test the hypothesis that the effects of the CBT-E/TAU on the EDE-Q scores are mediated by the putative mediators investigated (i.e., self-esteem, perfectionism and interpersonal problems), first, standardized residualized gain scores are calculated by removing the portion of mid-treatment scores on the mediators that can be predicted linearly by corresponding pre-treatment scores and the portion of post-treatment EDE-Q scores that can be predicted linearly by mid-treatment EDE-Q scores. Next, following the analytic steps outlined by Baron and Kenny [70] and Kraemer et al. [71] we will test the significance of the following paths using linear regression analyses: path a: the independent variable (i.e., CBT-E/TAU) must affect the mediator (i.e., pre- to mid-residualized change scores for self-esteem, perfectionism or interpersonal problems); path b: the mediator must affect the dependent variable (i.e., mid- to post-residualized EDE-Q change scores); path c: the independent variable must affect the dependent variable; and path c’: the *direct* effects of treatment on the dependent variable must be meaningfully reduced when including a hypothesized mediator in the model. When early process changes predict later outcome changes, it will be further tested whether this prediction remains significant also after controlling for autocorrelations (i.e., the correlations between early and late process changes) and synchronous correlations (i.e., the correlations between early process and early outcome changes) [72]. The significance of the indirect effect of treatment on EDE-Q scores through the putative mediators will be determined using a bootstrap approximation with 5000 iterations to obtain biased-controlled confidence intervals. In case of multiple significant mediators, the independent contribution of these mediators will be further explored using multiple mediation models.

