## Methods/design

### Design

We will execute a multicenter randomized controlled trial (RCT) with two equal-sized parallel groups at three specialized ED treatment centers from three regions in The Netherlands. Participants will be randomized into two groups (CBT-E versus TAU) stratified by ED center and type of ED. Measurements will take place at pretreatment, 6 weeks, 20 weeks, 40 weeks and 80 weeks, resulting in a 2 (group) × 5 (time) repeated measures factorial design. For an overview of the proposed flow of participants, see Fig. 1. The present study protocol was written in accordance with the Standard Protocol Items: Recommendations for Interventional Trials (SPIRIT) [28]; copies of the SPIRIT Checklist and figure have been included in Additional files 1 and 2.

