### Participants

Participants will consist of 132 adult outpatients aged from 18 years with an ED diagnosis according to DSM-5 and a BMI of between 17.5 and 40. They are recruited at the participating mental health centers: PsyQ/Parnassia Psychiatric Institute in The Hague will include 60 patients and PsyQ/Lentis Psychiatric Institute in Groningen and Rintveld/Altrecht Mental Health Institute in Zeist both 36 patients.

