*TAU*: the usual treatment given at the participating treatment sites is in general based on CBT, individually or in a group with elements of existing CBT treatment protocols [26, 27]. Depending on the site’s treatment policy, this may vary from low-intensity care (weekly sessions) to high-intensity care. This high-intensity care consists of two group sessions a day for 2 days of the week, sometimes supplemented with individual sessions due to coexisting psychopathology. Most of the times more than one discipline (psychologist, dietitian, psychiatrist) is involved in applying the treatment. The type of treatment provided is registered.

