### Sample size

In order to detect an absolute difference in recovery rate from ED of 25% (CBT-E: 50% versus TAU: 25%), a sample size of 66 patients per treatment condition is required to provide 80% power at two-sided *p* < 0.05 (intention-to-treat analysis). This means that at least 132 patients are needed for this study.

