### Randomization, treatment allocation and blinding

Randomization takes place after screening of the inclusion/exclusion criteria and signing of informed consent. The research assistant will randomly assign the participating patients to CBT-E or TAU, stratified by center and type of ED (AN, BN, BED, OSFED). Within each of the twelve strata, a research assistant will randomize participants using a permuted block design. Given the nature of the psychological treatment neither the therapists nor participants can be blinded for the delivered treatment.

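### Mediation paths b and c' and the bootstrapped indirect effect leave out centre, ED type and baseline EDE-Q, which could bias the mediator–outcome association

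*Protocol article*

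**What the plan says.** The Putative mediators section defines two residual scores. Mid-treatment mediator scores have the part predicted by the same measure at pre-treatment removed. Post-treatment EDE-Q has the part predicted by mid-treatment EDE-Q removed. Linear regressions then test path a (treatment on mediator change), path b ("path b: the mediator must affect the dependent variable (i.e., mid- to post-residualized EDE-Q change scores"), path c (treatment on outcome) and path c' (the treatment effect once the mediator is in the model).

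If early mediator change predicts later EDE-Q change, the prediction is retested while "controlling for autocorrelations (i.e., the correlations between early and late process changes) and synchronous correlations", that is, with late mediator change and early EDE-Q change held constant. The indirect effect is tested with 5000 bootstrap resamples. No other covariate is named in any of these models.

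Elsewhere the article treats site and diagnosis as important:
- Under Study conditions, TAU depends on site policy: "this may vary from low-intensity care (weekly sessions) to high-intensity care".
- The Background says that TAU differs between ED categories.
- Allocation is "stratified by center and type of ED (AN, BN, BED, OSFED".
- Under Primary study parameter(s), the logistic model for recovery includes baseline EDE-Q, and centre differences are examined in the EDE-Q multilevel model.

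**The concern.** Randomisation makes the arms comparable, so path a and the total effect (path c) are protected. It does not make patients whose self-esteem improved a lot by week 6 comparable with patients whose self-esteem improved little. Paths b and c' rest on that second comparison, so common causes of early mediator change and later EDE-Q change have to be controlled there.

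The article itself points to two candidates. A site that gives more intensive TAU, or a diagnosis that responds faster, could show more mediator change up to week 6 and more EDE-Q change from week 6 to week 20. The two changes would then be correlated even if the mediator did nothing. Removing prior levels of each score does not remove a factor that acts on both changes. The bootstrap resamples the same models, so it carries the same bias.

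At stake is the explanatory part of the trial: self-esteem, perfectionism or interpersonal problems could be reported as a route by which CBT-E works when the association partly reflects centre or diagnosis.

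**Working it through.** **Inputs from the article**
- Sample size: "a sample size of 66 patients per treatment condition is required to provide 80% power at two-sided", so 132 in total, in "two equal-sized parallel groups at three specialized ED treatment centers".
- Centres: one site "in The Hague will include 60 patients" and the other two 36 each (Participants).
- Strata: 3 centres × 4 ED types = 12.

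**The plan's own figure.** The mediation section gives no sample size, so the only figure to reproduce is the one for the primary outcome, an "absolute difference in recovery rate from ED of 25% (CBT-E: 50% versus TAU: 25"%). With mean proportion 0.375:

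n = [1.960·√(2·0.375·0.625) + 0.842·√(0.50·0.50 + 0.25·0.75)]² / 0.25² = 57.7, so 58 per arm.

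With the continuity correction: (57.7/4)·[1 + √(1 + 4/(57.7·0.25))]² = 65.4, so 66 per arm. The stated 66 is reproduced, and 132 is used below.

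**Size of the bias, by hand.** Assume centre and ED type together explain a share r² of the variance of both change scores, in the same direction, and that the true path b is 0. The induced standardised slope is about √r²·√r² = r². Its standard error with 132 patients and treatment in the model is about 1/√129 = 0.088. The two-sided 5% rejection rate is then about Φ(r²/0.088 − 1.96) + Φ(−r²/0.088 − 1.96):
- r² = 0.02: 0.02/0.088 = 0.23, rejection about 6%
- r² = 0.05: 0.05/0.088 = 0.57, rejection about 9%
- r² = 0.10: 0.10/0.088 = 1.14, rejection about 21%

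**Simulation.** N = 132, centres 60/36/36, allocation stratified by centre and ED type, residual scores built as the article describes, true b = 0, 3000 runs per setting. Further assumptions: ED-type mix 10/30/20/40%, treatment effects of 0.5 SD on mediator and outcome, and treatment included alongside the mediator.

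| Assumed share of both changes | Path b significant, as planned | With the article's further controls | With centre and ED type added | Paths a and b both significant, as planned |
|---|---|---|---|---|
| 0% | 4.8% | 4.9% | 5.0% | 4.1% |
| 5% | 8.9% | 8.5% | 4.6% | 7.3% |
| 10% | 18.3% | 16.9% | 4.9% | 15.3% |
| 20% | 53.0% | 44.7% | 5.3% | 43.5% |

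The mean spurious b was 0.051, 0.093 and 0.176 at 5%, 10% and 20%, and about 0 after adjustment. Other set-ups with the same N and centre sizes gave 8–11% at a 5% share, 20–21% at 10%, and 5–6% at 2%.

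**What a false mediator also needs.** With no treatment effect on the mediator and a 10% share, paths a and b were both significant in only 0.7% of trials.

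**Bootstrap.** The bias-corrected bootstrap of the indirect effect was significant in 12% and 23% of trials at 5% and 10%, but still in 9% after adjustment. Part of that excess therefore belongs to the bootstrap method and not to the omitted covariates.

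**If site acts only through TAU.** With 10–20% of TAU outcome variance due to site, path b was falsely significant in 10–23% of trials unadjusted, 7–10% with main effects only, and about 5% with centre × treatment added.

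**Cost of adjustment.** Two terms for centre, three for ED type and one for baseline EDE-Q make six degrees of freedom. Without confounding, power at b = 0.26 fell from 82.6% to 80.2%.

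**The case against.** The case on the other side has real force.

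- **Some adjustment is planned.** A reader might infer that the mediation models contain no baseline control at all. They do contain some: the mediator's pre-treatment score is removed, EDE-Q is residualised on its mid-treatment value, and a conditional retest adds early EDE-Q change and late mediator change. Stable differences in severity are largely dealt with. What remains is a factor that drives both changes, and the table shows that the retest removes little of that.
- **Path b alone does not declare a mediator.** In simulations with 0.5 SD effects and shares of 2%, 5% and 10%, paths a, b and c were all significant in 4.1%, 5.7% and 13.9% of trials. Requiring c' to fall by at least 20% as well gave 1.5%, 2.7% and 8.0%. This stands for the stepwise route. The separate bootstrap test has no path c requirement.
- **The confounder strength is assumed.** Variation in TAU intensity by site does not show that some sites change faster on both measures, and stratifying on ED type is not evidence of confounding. With the outcome loading halved at the 10% share, path b was significant in 8.3%. This stands.
- **The analysis is exploratory and the article is condensed.** Covariate detail may sit in a fuller document. But the section lists each model and its controls, so this is a stated choice that can be improved, not only an omission of detail.

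**Conclusion.** The point holds in limited form. Beyond the mediator's own pre-treatment score, and mid-treatment EDE-Q for the outcome, the mediation models control for no baseline characteristic. Centre, ED type and baseline EDE-Q are absent from paths b and c' and from the bootstrap.

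If centre and ED type explain 5–10% of both change scores, path b is falsely significant in about 9–20% of trials, against about 5% when they are included; at about 2% the inflation is negligible. These shares are assumptions, and so is the equal loading on both changes.

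A reader might go further and conclude that the trial is likely to report a false mediator, or that its effectiveness result is affected. The documents support neither. A false mediator also needs a treatment effect on the mediator, and in the stepwise route a significant path c. Path a and the total effect keep the protection of stratified randomisation, and the primary recovery comparison is untouched. This is a worthwhile, inexpensive improvement to an exploratory analysis.

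**What to change.** In the Putative mediators section, state that:
1. centre, ED type and baseline EDE-Q are covariates in paths b, c and c' and are refitted in every bootstrap resample;
2. the adjusted indirect effect is the main exploratory mediation result;
3. a model with centre × treatment is a sensitivity check, because TAU is set by site and main effects alone did not fully remove the bias in that case;
4. confounding of mediator and outcome by unmeasured factors remains possible, so mediation findings are read with that limit.

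This takes a few sentences and no new data, since all three covariates are already collected. The downside is about six degrees of freedom out of 132 patients and roughly 2 points of power when there is no confounding.

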### Procedure

Each patient will be recruited at the site at which they were referred for treatment. All assessors have been trained in the adjusted SCID-I ED section which will be used to diagnose Axis-I ED. During intake potential participants receive information about the research (treatment conditions, procedure, randomization process, confidentiality) from the local assessors. The assessment staff of each site will decide whether a patient meets the inclusion or exclusion criteria and whether they are definitely eligible for the study. If this is considered to be the case, the research assistant (who is located at the logistic center of the study, PsyQ The Hague) will, for each site, randomly assign the patient to TAU or CBT-E and send an email (in attachment) to the assessor. Randomization is done by making use of a random allocation program, stratified by center and type of ED. Participation will be discussed with the patient during a second appointment with the assessor. If the patient is willing to participate and has signed the Informed Consent Form, the assessor will open the email to inform the patient of the condition they are assigned to. Data will be obtained mainly by online questionnaires, with exception of the SCID-I ED section, which will be conducted by telephone, and the IAT computer task which will be conducted on a stand-alone computer. Prior to the first treatment session, patients will be asked to fill out the online questionnaires and complete the IAT computer task. After 6, 20, 40 and 80 weeks the online questionnaires are obtained. After 20 and 80 weeks the SCID-I will be repeated. After 20 weeks the IAT task will be repeated (for an overview of the assessments see Fig. 1). Participants who do not complete the online questionnaires within 1 week will be contacted by means of personalized emails and/or telephone calls. If they decide to discontinue study participation, efforts will be made to retain them in the trial, while respecting their right to withdraw from participation at any time without further consequences. Patients will not receive any monetary compensation for their involvement, but treatment will be delivered free of charge.

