### Study conditions

*CBT-E*: a transdiagnostic 20-session version of CBT, CBT-E(nhanced). In this study we use the focused version for patients with a BMI above 17.5, designed to be suitable for the full range of ED diagnoses. CBT-E is a treatment for ED psychopathology, rather than for a specific ED diagnosis. The strategy underpinning CBT-E is to construct a transdiagnostic formulation (or set of hypotheses) of the processes that are maintaining the patient’s psychopathology and to use this formulation to identify the features that need to be targeted in treatment. This formulation is constructed at the beginning of treatment, but will be revised ,if needed, during therapy. In this way a tailor-made treatment is created.

Stage 1 (sessions 1–7) is an intensive initial stage, with appointments twice a week. The therapist and the patient together set up the formulation of the underlying maintaining factors, which will be used as a base for the remainder of the treatment. The aims of this stage are to engage the patient in treatment.

Stage 2 (sessions 8–9) are weekly appointments. This stage is a brief stage in which the therapist and patient take stock, review progress, identify any emerging barriers to change, modify the formulation and plan stage 3. This stage is important to identify problems with the therapy, to remove barriers and adjust treatment if needed. After stage 2 the treatment will become more personalized.

Stage 3, (sessions 10–17) is the main body of treatment. There are eight weekly appointments. The aim is to address the main mechanisms that are supposed to maintain the patient’s ED. How this is done precisely varies from patient to patient. The therapist can choose to pay attention to one or more defined maintaining factors.

Stage 4 (sessions 18–20) is the final stage of treatment and the focus shifts to the future. The appointments are scheduled at 2-week intervals. There are two aims: the first one is to ensure that the changes are maintained (over the subsequent 20 weeks until a review appointment is held), and the second one is to minimize the risk of relapse in the long-term.

After 20 weeks there is a review session. The most important aim in this session is to review what has been learned and achieved during treatment and what risk factors are to be taken into account when therapy has ended.

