#### Putative predictors/mediators

*The Rosenberg Self-Esteem Scale (RSE).* The RSE is a widely-used 10-item Likert scale to measure self-esteem. Items are answered on a 4-point scale – from “strongly agree” to “strongly disagree” – measuring positive and negative feelings towards the self [58]. The Dutch version of the RSE is found to be a one-dimensional scale with high internal consistency (Cronbach’s alpha of 0.89) and congruent validity [59].

*Implicit Association Test Self-Esteem (IAT)* [60]. The IAT will be used to assess implicit self-esteem. The IAT is a computer-administered task, which measures the automatic associations between concepts. The IAT is based on a double discrimination task in which participants are asked to assign single stimuli as fast as possible to a given pair of target categories. The internal consistency has an average score of 0.70 [60].

*Frost Multidimensional Perfectionism Scale (F-MPS)* [61]. We will use the F-MPS to assess perfectionism. The scale contains 35 questions with a 5-point Likert scale from “strongly disagree” to “strongly agree.” When the scale was developed it measured six subscales of perfectionism. It is regarded as internally consistent, reliable over time and displays sound concurrent validity [61, 62]. However, in practical applications, the six-factor structure appeared to be unstable and an alternate four-factor structure was proposed by several others [63, 64].

*Inventory of Interpersonal Problems (IIP-32)* [65]. The IIP is a self-report questionnaire that measures the interpersonal problems that people experience. The instrument was first developed as a 127-item questionnaire on the basis of a list of common interpersonal difficulties raised by persons seeking psychotherapy. The 64-item version was created by Alden et al. [66] specifically to provide a circumplex measure (originally called the IIP-C). For this research we will use the shorter 32-item version (IIP-32), which was developed with the aim of providing a more rapid assessment with a good reliability and validity [67]. All items are rated on a 5-point Likert scale ranging from 0 (“not at all”) to 4 (“extremely”). The questionnaire has good internal consistency, the coefficient alpha for the scales of the IIP-32 are above 0.70 [65].

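### Mediation is made to depend on a treatment effect on EDE-Q change after week 6, a narrower outcome than the hypothesis, and the condition often fails when benefit comes early

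*Protocol article*

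**What the plan says.** The hypothesis in the Putative mediators section is that "the effects of the CBT-E/TAU on the EDE-Q scores are mediated by the putative mediators investigated", with no limit to any part of the treatment period. The outcome is then built by removing "the portion of post-treatment EDE-Q scores that can be predicted linearly by mid-treatment EDE-Q scores". Mid-treatment is week 6 and post-treatment is week 20 (Fig. 1 legend).

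The dependent variable is defined once, under path b: "path b: the mediator must affect the dependent variable (i.e., mid- to post-residualized EDE-Q change scores". The next requirement, "path c: the independent variable must affect the dependent variable", gives no other definition, so path c refers to the same week 6 to week 20 residual. Path c' adds that the direct effect must shrink to a meaningful degree once the mediator is in the model; no threshold is given. The section ends with a 5000-iteration bootstrap interval for the indirect effect. It does not say what follows if the bootstrap and the path conditions disagree.

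The mediators named there are "i.e., self-esteem, perfectionism and interpersonal problems", each scored as change from pre- to mid-treatment. The IAT appears elsewhere, under the joint heading Putative predictors/mediators ("The IAT will be used to assess implicit self-esteem"). The Procedure section schedules it before treatment and then once more: "After 20 weeks the IAT task will be repeated".

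**The concern.** The hypothesis concerns the whole effect on EDE-Q, but the gate concerns only the part that week-6 EDE-Q does not predict. The plan looks for mediator change before week 6 and discounts any EDE-Q benefit that arises over the same weeks.

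The CBT-E schedule makes early benefit possible. Stage 1 "is an intensive initial stage, with appointments twice a week", so sessions 1–7 take 7/2 = 3.5 weeks. Sessions 8–9 are weekly and add 2 weeks. That places 9 of 20 sessions within 3.5 + 2 = 5.5 weeks, before the week-6 measurement.

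At stake is a report of no mediation when the mediator does carry part of the effect, only because path c was not significant. The bootstrap test of the indirect effect does not need a significant path c, so the plan holds two standards that can conflict.

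**Working it through.** **The plan's own figure.** The article gives no power for path c. The only figure used here is 66 per arm (Sample size), which reproduces for 50% versus 25%, 80% power and two-sided 0.05. Without continuity correction, n = [1.96√(2 × 0.375 × 0.625) + 0.842√(0.25 + 0.1875)]² / 0.25² = 57.7, so 58. With the correction, (57.7/4)[1 + √(1 + 4/(57.7 × 0.25))]² = 65.4, so 66. The point does not touch it.

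**Assumptions.** Within-arm SD is 1 at each visit. The week-20 advantage is d = 0.5; the Discussion says only that the effect size is medium. The within-arm week 6 to week 20 correlation is r, and f is the share of the week-20 effect present at week 6. None of d, r or f is in the article.

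**Formulas (path c as written).**
- Pooled slope of week-20 on week-6 EDE-Q: s = (r + f·d²/4) / (1 + f²·d²/4)
- Effect left in the residual: c = d(1 − s·f)
- Residual SD within arm: √(1 − 2sr + s²); SE = SD × √(2/66) = SD × 0.174
- Power = Φ(c/SE − 1.96) + Φ(−c/SE − 1.96)

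**Example, r = 0.7, f = 1.** s = 0.7625/1.0625 = 0.718. c = 0.5 × (1 − 0.718) = 0.141. SD = 0.714 and SE = 0.124, so c/SE = 1.135 and power is 0.21. About 0.14 of the 0.5 SD effect remains: reduced, not removed.

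| Share present at week 6 | c (r = 0.7) | Formula power (r = 0.7) | Simulated (r = 0.7) | Simulated (r = 0.5 / 0.8) |
|---|---|---|---|---|
| all | 0.14 | 21% | 20% | 35% / 15% |
| four-fifths | 0.21 | 40% | 38% | 48% / 38% |
| half | 0.32 | 73% | 71% | 69% / 80% |
| none | 0.50 | 98% | 98% | 91% / 100% |

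**Comparator.** For week-20 EDE-Q adjusted for baseline with an assumed correlation of 0.5, c/SE = 0.5/(√0.75 × 0.174) = 3.32 and power is about 91% (about 90% simulated). For baseline correlations of 0.4 to 0.6 the simulated range is 87–95%, whatever the timing.

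**What the gate does to mediation itself.** The comparison above is between two tests of the treatment effect, so mediation was simulated separately, with joint significance of paths a and b standing in for the bootstrap and with assumed path strengths. Where the mediator also acts after week 6, paths a and b are both significant in about 90–98% of trials, but only 18–27% also pass path c. Where the mediator acts wholly through EDE-Q change by week 6, paths a and b with week-6 EDE-Q adjusted find it in only about 5%. Dropping the gate helps in the first case and not in the second.

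**The case against.** The lagged outcome is deliberate. Early process change is related to later outcome change to fix the time order, and the plan adds checks for autocorrelation and for early outcome change. That stands, and it is a good reason to keep the lagged outcome for path b. It is no reason to make path c on that outcome a condition.

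A reader might infer that CBT-E is front-loaded and that path c must therefore fail. The article does not support this. Session counts do not show when the between-arm difference arises. Study conditions describes stage 1 as aimed at engagement and stage 3, sessions 10–17, as the main body of treatment; those sessions come after the first 5.5 weeks. TAU is also active and largely CBT-based. If half or none of the effect is present at week 6, path c passes in 69–100% of trials across the correlations tried.

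A reader might also infer that the overall EDE-Q effect goes untested, or that the bootstrap is run only if path c passes. The first is wrong: the multilevel analysis covers EDE-Q from pre-treatment to the second follow-up. The second is not stated; the article leaves the relation between the two open.

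Finally, a reader might infer that the mediation plan names a mediator it cannot measure. The Putative mediators section never names the IAT. Its heading elsewhere covers predictors as well, and explicit self-esteem (RSE) is collected at week 6 with the other online questionnaires. Only a clarification of the IAT's role remains.

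**Conclusion.** The point holds as a mismatch between hypothesis and decision rule. Paths c and c' are worded as requirements on an outcome narrower than the effect to be explained. Under the stated assumptions the chance of passing path c ranges from about 20% to 98% at r = 0.7, depending on how much of the effect is present at week 6, against about 90% for the baseline-adjusted week-20 outcome. The condition often fails when the effect is early; it does not fail by construction. The sizes rest on assumed d, correlations and timing. The article presents mediation as exploratory and already concedes that only medium to large mediation effects can be tested with 80% power. The primary analysis and sample size are unaffected.

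**What to change.** In the Putative mediators section:

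1. Drop paths c and c' as conditions; report them descriptively if wanted. Judge mediation on the planned 5000-iteration bootstrap interval for the indirect effect.
2. Report the total effect as the treatment difference in week-20 EDE-Q adjusted for baseline EDE-Q.
3. Keep the lagged outcome for path b, but fit treatment, baseline mediator, mid-treatment mediator and week-6 EDE-Q in one model instead of pre-computed residuals, because week-6 EDE-Q is itself affected by treatment.
4. State that this estimates only mediation of change after week 6, so that mediation acting wholly through EDE-Q change by week 6 is not tested.
5. State that the IAT, measured at baseline and week 20, cannot enter the pre-to-mid mediator analysis and serves as a predictor, with the RSE as the self-esteem mediator.

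The cost is wording and analysis code. No new data or patients are needed. The change should be made before outcome data are examined by arm.
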